***Intermediate indicators***

Intermediate indicators for the prevalence of diarrhea in children include the hand-washing behaviors of caregivers at 4 critical times (before cooking, after defecating, before feeding the child, before eating). An intermediate indicator for child malarial prevalence is the utilization of insecticide bed nets the previous night while sleeping.

***Process indicators***

We are going to carry out a process evaluation along with the impact evaluation to investigate dose delivered and dose received. First, logbooks will be recorded by recorded by CHVs themselves and signed by caregivers, where we can assess how many key messages have been delivered at each household level. Second, four rounds of household survey will be conducted, with which we will measure how many and what key messages caregivers could recall.

***Sample size calculation***

Based on a preliminary survey in 2013, we estimated that the malaria prevalence was 25% and assumed that the prevalence would be reduced by our intervention by 25%, based on systematic reviews.^33^ Assuming a coefficient of variation of 0.16, a 10% loss to follow-up, a study power of 80%, a 25% prevalence of malaria in the absence of an intervention, and a 25% relative decrease after the intervention resulted in the need for 20 clusters and 950 household per arm, using a formula published elsewhere.^34^

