***Primary endpoint***

This study aims to assess the effect of CHVs on multiple child health outcomes. The primary endpoints of the study are the prevalence of diarrhea and fever/malaria among children under 5 years of age, and the proportion of children receiving case management for diarrhea and malaria. We plan to use the 14-day prevalence of reported diarrhea and the 14-day prevalence of fever/malaria in the household as indicated in caregiver’s reports.

For the case management for diarrhea, we will investigate whether a child with diarrhea has been administered ORS. For malaria, we will measure whether a child with malaria symptoms was tested using an RDT kit and whether he or she was referred to a health facility if diagnosed with malaria.

The survey will be conducted three times at the household level: the first and second round will be carried out in the first phase, and the final round will be carried out in the second phase.

Diarrheal is defined as 3 or more instances of watery stools within 24 hours over the last 14 days. Febrile episodes will be assessed as a proxy indicator of malarial prevalence based on caregiver reports.

The main outcomes and indicators are presented in Table 1.

Table 1. Main outcomes and indicators.

| **Indicator (%)** (Denominators are within the respondents of the household survey) | | |
| --- | --- | --- |
| Use of ORS among under-5 children with diarrhea | Numerator | Number of U5C^1^ who took ORS^2^ when experiencing diarrhea over the past 14 days |
|  | Denominator | Number of U5C who experienced diarrhea in the past 14 days |
| Prevalence of diarrhea in under-5 children | Numerator | Number of U5C who experienced diarrhea in the past 14 days |
|  | Denominator | Number of U5C |
| Diagnosis rate of malaria in under-5 children using an RDT | Numerator | U5C diagnosed with RDT for malaria in the last two weeks |
|  | Denominator | U5C who have complained of fever in the last two weeks |
| Malaria incidence in under-5 children | Numerator | U5C who have complained of fever in the last two weeks |
|  | Denominator | Number of U5C |

^1^ U5C, under-5 children; ^2^ ORS, oral rehydration solution

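### The 950 households per arm appear to leave out the listed 10% loss, so power is about 76% to 78% rather than 80%, and only fever/malaria among the primary endpoints was sized

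*Protocol*

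**What the plan says.** The Protocol's Sample size calculation section takes "a 25% prevalence of malaria in the absence of an intervention" and "a 25% relative decrease after the intervention". It continues "Assuming a coefficient of variation of 0.16", then adds "a 10% loss to follow-up" and "a study power of 80" per cent. Together these "resulted in the need for 20 clusters and 950 household per arm, using a formula published elsewhere". The formula cited is the simple sample size method for cluster-randomized trials in the References. The section gives no significance level and counts households, not children.

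The Primary endpoint section is wider: "The primary endpoints of the study are the prevalence of diarrhea and fever/malaria among children under 5 years of age", and it adds the proportions of affected children who receive case management for diarrhea and for malaria. Table 1 lists four indicators. Malaria is measured there by caregiver-reported fever. The Discussion describes the cluster and household numbers as adequate, without limiting this to one endpoint.

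**The concern.** Because the 10% loss is listed among the inputs, 950 reads as an enrolment figure that already allows for it. If so, about 855 households per arm would be analysed, and these should give 80% power. If the loss was left out, the stated power is not delivered on the stated assumptions.

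The second issue is coverage. The Protocol ranks diarrhea prevalence and the case-management proportions alongside fever/malaria prevalence, but only the latter was sized. A reader who takes 80% as the power of the whole primary set could read a null diarrhea result as evidence that volunteers have no effect on diarrhea, when the trial may simply have had too little power to show one.

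**Working it through.** **Inputs**

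- From the Sample size calculation section: p0 = 0.25; p1 = 0.75 × 0.25 = 0.1875; k = 0.16; loss 10%; 20 clusters and 950 households per arm.
- Assumed, because not stated: two-sided 5% (z = 1.960) and one analysed child per household. For 80% power, z = 0.8416.
- From Table 2: 999 and 957 caregivers surveyed; diarrhea in the last-born child 17.5% and 20.1%; fever 29.4% and 35.2%.

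**Formula** (unmatched clusters, proportions, m analysed per cluster)

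c = 1 + (1.960 + 0.8416)² × V / (p0 − p1)², where V = [p0(1 − p0) + p1(1 − p1)]/m + k²(p0² + p1²).

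Power = Φ( √[(c − 1)(p0 − p1)²/V] − 1.960 ).

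The fixed parts are:

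- p0(1 − p0) + p1(1 − p1) = 0.1875 + 0.1523 = 0.3398
- k²(p0² + p1²) = 0.0256 × (0.0625 + 0.0352) = 0.0025
- (p0 − p1)² = 0.0625² = 0.003906
- (1.960 + 0.8416)² = 7.849

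**Step 1: the Protocol's figure, loss ignored.** m = 950/20 = 47.5.

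- V = 0.3398/47.5 + 0.0025 = 0.009655.
- Clusters needed = 1 + 7.849 × 0.009655/0.003906 = 20.4 (19.4 without the +1).
- Power with 20 clusters = Φ(2.773 − 1.960) = 79.2% (81.2% without the +1).

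This is close to the published design.

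**Step 2: loss applied.** m = 950 × 0.9/20 = 42.75.

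- V = 0.3398/42.75 + 0.0025 = 0.010450.
- Clusters needed = 22.0 (21.0 without the +1).
- Power with 20 clusters = Φ(2.665 − 1.960) = 76.0%. Without the +1 it is Φ(2.734 − 1.960) = 78.1%.
- Cross-check by design effect: intracluster correlation = k²p0/(1 − p0) = 0.0085, power 76.6%.

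**Step 3: size needed for 80% with 20 clusters.**

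- V must be 19 × 0.003906/7.849 = 0.009456.
- So m = 0.3398/(0.009456 − 0.0025) = 48.86, or 977 analysed per arm.
- Enrolment = 977/0.9 = 1,086 per arm. Without the +1 it is 912 analysed and 1,013 enrolled.
- If 950 was meant as the analysed number, enrolment should be 950/0.9 = 1,056.
- The first round surveyed 999 and 957. Less 10%, these leave 899 and 861, with power about 76.8%.

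**Step 4: diarrhea prevalence.** The Protocol gives no effect size or k for diarrhea, so the 25% reduction and k = 0.16 are borrowed from the malaria calculation. m = 42.75.

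| p0 | p1 | V | √[19(p0 − p1)²/V] | Power |
|---|---|---|---|---|
| 0.175 | 0.1313 | 0.00727 | 2.237 | 61% |
| 0.201 | 0.1508 | 0.00837 | 2.395 | 67% |

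**Step 5: case management.** The denominators are affected children only. In the first round there were 175 and 192 with diarrhea, and 294 and 337 with fever. These are far below 950, and no calculation is given for either proportion.

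**The case against.** The strongest reply is that the gap is small and depends on what the Protocol leaves unstated.

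- **Children per household.** The Eligibility section admits households with one or more under-5 children, and Table 1 counts children. At 1.15 analysed children per household, power after loss is 80.2%, ignoring clustering within households. This stands as a limit. However, Table 2 reports the last-born child only, so one child per household is the more natural reading.
- **Alpha.** One-sided 5% would give 84.6% after loss. It would also need only about 795 enrolled per arm, so it does not explain 950.
- **The +1 term.** Without it, 950 analysed households need 19.4 clusters, which rounds to the stated 20. That again fits only if the loss is left out; with the loss, power is 78.1%.
- **Observed fever.** At the first-round rates of 29.4% and 35.2%, with the same relative fall, k and loss, power is about 82% and 88%. This softens the practical consequence for fever. It does not make the stated calculation correct on its stated 25%.

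Three stronger readings are tempting, and the documents do not support them.

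- A reader might infer that the primary endpoints will be tested without error control. Multiplicity handling is commonly left to an analysis plan, and that plan is not shown, so its absence here is not a fault.
- A reader might infer that power for fever collapses because only malarial fevers would fall. That needs the malarial share of fevers, which the Protocol does not give. The Protocol also openly treats fever as a proxy, in the Primary endpoint section and in the Discussion.
- A reader might conclude that fever, as the only sized endpoint, should become the single primary and gate the others. That is a debatable trade-off for a trial that aims at several child health outcomes, and nothing in the Protocol requires it.

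**Conclusion.** The point holds in a limited form. With the cited formula and the Protocol's own inputs, 950 households in 20 clusters per arm come close to 80% power only when the listed 10% loss is not deducted. After the loss, power is about 76%, or 78% without the +1 term: a shortfall of 2 to 4 percentage points. This rests on two-sided 5% and one analysed child per household. It is not a flat failure to reach 80% under every reading, since slightly more than one analysed child per household would restore it.

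The gap in coverage is larger. Only fever/malaria prevalence was sized. Diarrhea prevalence has roughly 61% to 67% power if the malaria effect and k carry over, and the two case-management proportions have no calculation at all. This matters for how null results are read; it does not invalidate the design.

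**What to change.** In the Sample size calculation section:

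1. Restate the power as about 76% to 78% after 10% loss for a fall from 25% to 18.75%. The alternative is to present 950 as the analysed number, with about 79% power. In that case the loss statement must be reconciled with the 999 and 957 surveyed, because these less 10% fall below 950.
2. State the significance level and its sidedness, and how many children per household are analysed.
3. Say that the calculation covers caregiver-reported fever only, and that the other primary endpoints were not sized.
4. Give the approximate diarrhea power (about 61% to 67% after loss, same relative effect and k assumed), so that a null diarrhea result is not taken as evidence of no effect.

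No extra households or clusters are needed. The cost is a slightly less favourable stated power and a few added sentences.

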***Household sampling methods***

The demographic information of each community in the Ketu South district was compiled by the health directorate through reports by CHNs in each CHPS zone prior to the baseline survey. The total number of communities in the Ketu South district was 57, and we applied the probability-proportionate-to-size method to select 40 communities (See Figure 2). We excluded urban area for the trial since CHV may operate differently between urban and rural areas.

***Eligibility criteria and randomization***

Forty communities were assigned into 8 strata on the basis of the prevalence of diarrhea in under-five children, economic status of the community, and the proportion of mothers who delivered their youngest child by a skilled birth attendant based on the results of the first-round survey. To evaluate the socioeconomic status of a community, we used the proportion of households with wattle and daub houses as representatives of the lowest economic level. We ensured that an equal number of communities within all 8 strata were randomly allocated into the intervention and control arms, with each arm including 20 communities. Microsoft Excel version 15.22 was used for randomization. We ensured comparability in the main outcomes between the intervention and control arms by strictly applying randomization. After conducting the first-round survey, we classified the clusters into strata by primary endpoint and socioeconomic status. In doing so, we were able to ensure a high comparability and therefore were able to avoid selection bias. Control communities are allocated by randomization among the target communities. We found control and intervention communities well balanced in terms of caregivers’ demographic and socioeconomic status, and child demographic status and several key variables related to primary outcomes of the intervention (Table 2).

Figure 2. Flow diagram of the trial.

| [figure not shown] |
| --- |

Table 2. Results of the first-round survey in the intervention and control arms.

| **Variables** | | **Intervention** | | **Control** | |
| --- | --- | --- | --- | --- | --- |
|  |  | N | % or  mean (SD^2^) | N | % or  mean (SD) |
| Caregiver's age (years) | | 999 | 29.00(7.16) | 957 | 28.86(6.78) |
| Religion of respondent | Christian | 614 | 61.50% | 599 | 62.60% |
|  | Traditionalist | 280 | 28.00% | 256 | 26.80% |
| Education level of respondent | Graduated basic school | 188 | 23.6% | 165 | 22.5% |
|  | Dropped out of basic school | 455 | 57.2% | 406 | 55.3% |
|  | Graduated secondary school | 19 | 2.4% | 24 | 3.3% |
| Possession of NHIS^1^ Card | Have a valid card | 332 | 33.2% | 328 | 34.3% |
| Age of the youngest child under-5 child (In months) | | 989 | 22.97 (15.95) | 946 | 21.97 (15.94) |
| Youngest child’s sex | Male | 505 | 50.6% | 483 | 50.5% |
| Main source of drinking water for the last-born child | Hand-dug well | 268 | 26.8% | 248 | 25.9% |
|  | Sachet water | 202 | 20.2% | 223 | 23.3% |
|  | Borehole | 190 | 19.0% | 141 | 14.7% |
|  | Bottled water | 163 | 16.3% | 150 | 15.7% |
|  | Public standpipe | 70 | 7.0% | 96 | 10.0% |
| Possession of Child Health Record Book | | 689 | 69.0% | 671 | 70.1% |
| Most recently measured weight of the last-born child | Average weight (kg) | 689 | 9.14(2.60) | 671 | 8.92(2.66) |
| Diarrhea incidence in the last-born child | | 175 | 17.5% | 192 | 20.1% |
| Provision of ORS to the last-born child having diarrhea | | 94 | 53.7% | 97 | 50.5% |
| Febrile episode in the last-born child | | 294 | 29.4% | 337 | 35.2% |
| Child had malaria test when febrile | | 55 | 17.7% | 57 | 16.9% |

^1^ NHIS: National Health Insurance Scheme; ^2^ SD: standard deviation.

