***Data analysis***

Intention-to-treat analysis will be conducted to explore the effect of CHV activation on childhood infectious disease of under-five children. For diarrheal prevalence as a dependent variable, water quantity and quality, hygiene behavior of caregivers, presence of improved latrines, characteristics of the enrolled child such as age and sex, household income, and caregiver’s education level will be controlled for in quantifying the net effect of CHVs. For malaria prevalence as a dependent variable, the enrolled child’s characteristics, household income, and caregivers’ education level will be controlled. Environmental risk factors such as seasonality and altitude are also considered to be independent variables for malaria prevalence. However, the intervention and control arms in our study site present no difference in those factors so there will be no control for environmental factors. When quantifying the net effect of CHVs on child malaria prevalence, insecticide-treated bed net utilization will not be controlled since it is considered an intermediate factor between intervention and disease outcome. Generalized estimating equations will be used for investigation at the cluster level. The random effects model will be used, taking account of between-cluster variation by assuming that there are cluster-level effects. Per-protocol analysis will be performed to obtain additional background information if the overall percentage of CHVs activated does not reach 80%. Multi-level analysis will also be conducted to explore whether the effects of CHVs on child diarrheal and malaria prevalence vary by community depending on a community’s overall coverage of activated CHVs.

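### Round-1 fever, the malaria endpoint, was 29.4% in the intervention arm and 35.2% in control; the protocol calls the arms well balanced and its malaria model omits round-1 fever

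*Protocol*

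**What the plan says.** In the Protocol, *Eligibility criteria and randomization* states that comparability in the main outcomes was secured by randomization. It then reports: "We found control and intervention communities well balanced in terms of" demographic, socioeconomic and outcome-related variables, with Table 2 as the evidence. The Table 2 row for the malaria endpoint reads: "Febrile episode in the last-born child | | 294 | 29.4% | 337 | 35.2" (percent).

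The same section names three stratification factors: community diarrhea prevalence, economic status and skilled delivery. Fever is not among them, although it was measured in the same survey before allocation.

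*Primary endpoint* makes caregiver-reported fever over 14 days the proxy for malaria. *Sample size calculation* takes malaria prevalence without CHVs to be 25% and concludes: "a 25% relative decrease after the intervention resulted in the need for 20 clusters and 950 household per arm".

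*Data analysis* sets the adjustment: "For malaria prevalence as a dependent variable, the enrolled child’s characteristics, household income, and caregivers’ education level will be controlled". The only examples of child characteristics, given in the preceding sentence on diarrhea, are age and sex. No round-1 fever, baseline cluster prevalence, change from baseline or arm-by-round contrast is named.

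**The concern.** The outcome that drives the sample size differs between arms before any intervention, in the direction of benefit. The text describes the arms as comparable, and the stated model has no term to absorb the difference. If communities with more fever at round 1 tend to have more fever at round 2, part of the starting gap will appear in the estimated effect.

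This is more than detail left to an analysis plan. The protocol fixes a covariate list for malaria and argues for what it leaves out: environmental factors are dropped because the arms are said not to differ on them. Observed balance is thus used to decide on adjustment, while the visible difference in the endpoint itself goes unmentioned.

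**Working it through.** **Inputs.** From *Sample size calculation*: "Assuming a coefficient of variation of 0.16, a 10% loss to follow-up, a study power of 80" percent; p0 = 0.25, and a 25% relative reduction gives p1 = 0.1875. From Table 2: 294 and 337 febrile children. The fever row prints no denominators; 999 and 957 come from the caregiver-age row, "999 | 29.00(7.16) | 957 | 28.86(6.78", and they return the printed percentages. Alpha is not stated; two-sided 0.05 is assumed.

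**1. The plan's own figure.** The formula is cited only ("using a formula published elsewhere"). The usual unmatched cluster formula is c = 1 + (1.96 + 0.84)² × [p0(1−p0)/m + p1(1−p1)/m + k²(p0² + p1²)] / (p0 − p1)². With m = 950/20 = 47.5 it gives c = 20.4 and 79% power, so the stated 20 clusters and 950 households reproduce closely if 950 is the number analysed. The planned effect is 25 − 18.75 = 6.25 points.

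**2. The round-1 gap.**
- 294/999 = 29.4%; 337/957 = 35.2%; difference 5.8 points, ratio 0.84.
- Relative scale: 5.8/35.2 = 16.4%, against the planned 25%: about two thirds.
- Absolute scale: 5.8/6.25 = 93%. But 6.25 points assumes 25% control prevalence. At 35.2%, a 25% reduction is 8.8 points, and 5.8/8.8 = 66%.

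**3. How unusual the gap is.**
- Ignoring clustering: z = 2.74, p = 0.006.
- With clustering, variance = a(1−a)/999 + b(1−b)/957 + k²(a² + b²)/20, where a and b are the two proportions. At k = 0.16: 0.000208 + 0.000238 + 0.000270, SE 2.7 points, z = 2.16, p ≈ 0.03.
- At an assumed k = 0.25: SE 3.3 points, z = 1.74, p ≈ 0.08.

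These p-values describe the size of the gap. They do not test whether the randomization was sound.

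**4. How much should persist.** Pooled fever is 631/1956 = 32.3%, with 1956/40 ≈ 49 children per cluster. The between-community variance is (0.16 × 0.323)² = 0.00266. The sampling variance of a cluster prevalence is 0.323 × 0.677/49 = 0.00446. The stable share is 0.00266/(0.00266 + 0.00446) = 37%, if community effects do not change between rounds. The expected carry-over is 0.37 × 5.8 = 2.1 points.

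**5. Consequence with no true effect.** The round-2 SE is √{[2p(1−p)/42.75 + 2k²p²]/20}, with 42.75 = 0.9 × 950/20.
- p = 0.25: √[(0.00877 + 0.00320)/20] = 2.4 points.
- p = 0.32: √[(0.0102 + 0.0053)/20] = 2.8 points.

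The rejection rate is Φ(−1.96 + d) + Φ(−1.96 − d), with d = 2.14/SE. It is about 14% at SE 2.4 and 12% at SE 2.8, instead of 5%. This is approximate: it uses the full design SE for the spread of the estimate, although fixing the round-1 result would narrow that spread and lower the rate a little.

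**6. The adjacent Table 2 row.** Malaria tests among febrile children are given as 55 (17.7%) and 57 (16.9%). Control agrees: 57/337 = 16.9%. Intervention does not: 55/294 = 18.7%, whereas 55/0.177 ≈ 311. With 311/999 = 31.1%, the gap is 4.1 points, naive p = 0.055 and clustered p ≈ 0.13 at k = 0.16. The carry-over is then 0.37 × 4.1 = 1.5 points, and the rejection rate in step 5 becomes about 8 to 9%.

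**The case against.** - **Randomization was valid.** Communities were stratified and allocated at random, so over all possible allocations the test without baseline adjustment keeps its nominal error rate. This stands. A reader might infer a faulty allocation or a systematically biased design; the documents support neither. The inflation applies only given the allocation that was drawn.
- **The size is easily overstated.** A reader might take the gap as almost the whole planned effect (93% in points), or assume that all of it persists, which would give a false-positive rate of 55 to 66%. The plan states its effect as a relative reduction, on which the gap is about two thirds. Full persistence conflicts with k = 0.16, and the endpoint is a 14-day recall measure that the *Discussion* concedes varies by season. A larger k would raise persistence but would also make the gap less unusual.
- **The fever count is uncertain.** The two Table 2 rows disagree, and the document does not show which figure is wrong. This stands and limits confidence in the 5.8 points.
- **Diarrhea leans the same way** (17.5% versus 20.1%), which tempts a wider claim. But diarrhea prevalence was a stratification factor, and the gap is within chance: naive p = 0.15, about 0.20 with k = 0.16.
- **The analysis plan may settle it.** An unseen plan could add baseline fever or model round 1 as a repeated outcome, and the protocol forbids neither. Still, its own list is specific and omits the term.
- **The wording is narrow.** The balance sentence says several key variables, and the fever figures are openly tabulated. Nothing is hidden, but the sentence points to the table that shows the gap, and the section separately claims comparability in the main outcomes.

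**Conclusion.** The point holds in limited form. The balance description does not fit fever, and the malaria covariate list omits the one baseline variable most directly tied to that endpoint. The gap is 5.8 points as tabulated (16% relative), or 4.1 points if the testing row is right.

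With k = 0.16, stable community effects and no true effect, the chance of a significant result without round-1 adjustment is about 12 to 14%, or 8 to 9% with the smaller gap. These figures rest on two-sided 0.05, the planned sample after 10% loss, and the protocol's k. They are conditional on this allocation.

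The documents do not support saying that a positive fever result would be uninterpretable, that randomization failed, or that the diarrhea comparison is compromised. The case for change is that the adjustment uses data already collected and removes an avoidable doubt about a primary outcome.

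**What to change.** 1. In *Data analysis*, prespecify round-1 fever as a covariate in the malaria prevalence model: the cluster's round-1 prevalence, plus the household's own round-1 response where available. Keep the model without it as a sensitivity analysis. Give its prognostic value as the reason, not a baseline significance test.
2. In *Eligibility criteria and randomization*, replace the well-balanced statement with one saying that fever was lower in the intervention arm at round 1 and is adjusted for. Qualify the claim of comparability in the main outcomes accordingly.
3. Reconcile the fever and malaria-test rows of Table 2 for the intervention arm against the survey data, and restate the gap if the count changes.
4. Optionally, add round-1 cluster prevalence to the diarrhea model for precision. Household-level baseline adjustment should not be extended to the case-management outcomes, which are measured only in ill children, so many households have no round-1 value.

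The cost is wording, one model term and a check of one table row. No new data are needed. The change should be dated before follow-up outcomes are analysed by arm.
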